#### Inclusion and exclusion criteria

Inclusion criteriaDocumented HIV infectionEnrolled in HIV care and taking ART at a designated ACT study siteAge 13–17 years: this allows for the following: alignment with target ages for routine transfer for healthcare facilities in Nigeria of 15- and 18-year-olds [14]; the pre-transfer 12-month transition period plus organized support group in the IG while CG is simply observed; and flexibility (albeit limited) in recruitment and study transfer age given the observed flexibility in age at transfer in actual practiceAware of HIV diagnosis

Exclusion criteriaUnable or unwilling to provide assent/consentNot medically stable

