In the intervention arm, ALHIV will be transitioned from pediatric to adult care over a period of 1 year. Participants will be enrolled when they are approximately 1 year younger than the routine age of transfer at each study facility (either 15 or 18 years of age). During the 12-month pre-transfer period, ALHIV will be scheduled for clinic visits per the PAPA model. Patient advocates will accompany adolescents to each PAPA clinic visit. In addition, ALHIV receiving care at intervention sites will be encouraged to attend monthly OSG meetings. OSG meetings will be scheduled with routine clinic visits and at adolescent-friendly times to minimize logistical problems and to increase attendance and sustainability. Each OSG will include up to 25 participants.

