### Description of the control condition/usual care

The usual “transition” of care for ALHIV in Nigeria is abrupt transfer to adult care. For this protocol, “transfer” is defined as immediate handover of the ALHIV from pediatric to adult care, without a transition period, and no formal or documented communication between pediatric and adult providers prior to, or after transfer. There is also no structured pre-transfer education and/or counseling provided to ALHIV and their caregivers with respect to procedures and expectations in adult care. In CG clinics, ALHIV will stop accessing pediatric care and start accessing the adult HIV clinic at the routine age of transfer at the facility. Adolescents will have access to all available services at the adult clinic including any adult support groups that may be available.

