### Outcome measures

The primary outcome measure is the *proportion of ALHIV retained in care at 12 and 24 months post transfer.* For this study, retention is defined as having made at least two clinic visits separated by a 6-month period within 12 months and at least four visits each separated by at least 6 months within 24 months post transfer. Hence, there are two primary outcome measures, with the long-term (24-month) retention measurement being a necessary “composite” of those who would have already demonstrated short-term (12-month) retention.

Secondary outcome measures are as follows:
*Proportion of ALHIV achieving viral suppression measured at 12 and 24 months post transfer*. Viral suppression is defined per the 2016 Nigerian national HIV guidelines as < 20 copies of HIV ribonucleic acid (RNA) per milliliter of blood plasma after at least 6 months of taking ART [33]
*Proportion of ALHIV demonstrating psychosocial wellbeing during study follow-up.* This study team has previously reported that poor psychosocial wellbeing and lack of adequate coping/self-efficacy skills are potential barriers to successful outcomes, including transitioning for this population in Nigeria [22, 34]. In order to generate more comprehensive evidence on wellbeing and resilience among ALHIV, we will administer four questionnaires among our study cohort: (1) the Health Locus of Control (HLC) scale will assess the extent to which ALHIV consider their health and health decisions to be within, or outside of their control; (2) the Mental Health Continuum-Short Form (MHC-SF) will measure the constructs of social, emotional, and psychological wellbeing; (3) the Functional Social Support Questionnaire (FSSQ) will evaluate the strength of the social support network of ALHIV; and (4) the psychosocial determinants of sexual risk behavior using the Sexual Risk Behavior, Beliefs, and Self-efficacy (SRBBS) scale will investigate for key psychosocial variables affecting ALHIV sexual risk-taking or protective behaviors [34–40]

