### Sample size estimation

The design requires two arms (control = direct transfer without transition period or OSG and intervention = graduated transition with OSG). Six geopolitical zones are included in the design, with two sites (one replicate per arm) located in each zone. The factors considered for the sample size estimate are: at least 80% power, assuming 20% effect size, a confidence level of 95%, a correlation among repeated measures of 0.3, and an intra-class correlation within clusters of 0.05. Further, we assume equal numbers of clusters between CG and IG, and clusters within those conditions to be of equal size. Based on these assumptions, a baseline number of 15 participants per site was needed. This was, however, adjusted for several assumed losses. Based on knowledge of healthcare in this area and among target participants, the following participant loss estimates were made: healthcare transfers out of study sites at 5%, participant moving out of study area at 5%, deaths during the study at 7%, and study withdrawal/dropout at 5%. This results in a total of 22% dropouts, requiring an additional three participants (15 × 0.22) for a total of 18 participants per site. Additionally, we anticipate a 30% rate for declining to participate. Hence, we will need to approach an additional five ALHIV (18 × 0.3) for a total of 23 ALHIV currently enrolled as taking ART at study initiation to ensure that the requirement of 18 participants per site is met. Therefore, for two arms across six zones, we have a recruitment goal of 276 ALHIV (23 × 2 × 6) with a desired final sample size of 216 ALHIV (18 × 2 × 6) consented to participate. Sample size estimation was performed using G*Power (v. 3.1.9.1, Universität Düsseldorf, Germany) and Sampsize (v 0.6, P. Glaziou, ampsize.sourceforge.net) with appropriate adjustments for cluster randomization [44].

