### Statistical analysis

For the primary objective, the study will assess the differential impact that the ACT intervention has on the primary outcome of retention. For this measure, ACT will test the difference in the percentage of study participants completing scheduled clinic visits under the hypothesis that the IG’s percentages will exceed CG percentages from baseline to 12 months (“short-term” retention) and to 24 months (“long-term” retention) following transfer to adult care. An initial test of proportions will be conducted at each time period to compare these percentages using a one-way test, and exact *p* values will be calculated using a permutation distribution. Additionally, a Poisson regression model with a time offset will be explored, which will allow for the development of a model to compare rates between the control and intervention arms while accounting for events (i.e., retention) per unit time, which allows time to vary for each subject as well as allowing the inclusion of potential covariates (for example, age, and time since HIV diagnosis).

Similarly, for secondary objective 1, the study will assess the differential impact that the intervention has on viral suppression. For this measure, ACT will test the difference in the percentage of study participants achieving viral suppression, under the hypothesis that the IG percentages will exceed CG percentages at each time period. The strategy in this analysis is similar to that of the primary objective: a one-way test of proportions will be conducted initially, followed by a Poisson count model to account for potential covariates of interest in addition to a temporal component.

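### Retention is counted from transfer, under timing rules that conflict, and the sample size treats deaths and withdrawals as replaceable losses, so the comparison is open to bias

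*Protocol article*

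**What the plan says.** **Outcome.** The Protocol article (Outcome measures) makes the primary measure the "proportion of ALHIV retained in care at 12 and 24 months post transfer". Short-term retention means "having made at least two clinic visits separated by a 6-month period within 12 months", and the 24-month definition builds on it. The clock starts at transfer.

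**When transfer happens.** Five places bear on this:
- The Abstract, Data collection and Table 1 give all participants 12 months before transfer and 24 months after. Table 1 keeps controls in the pediatric clinic through month 12 and shows them in the adult clinic from month 15.
- Description of the ACT intervention, in a paragraph opening with the intervention arm, says "ALHIV will be transitioned from pediatric to adult care over a period of 1 year" and then "Participants will be enrolled when they are approximately 1 year younger than the routine age of transfer at each study facility". The support group begins at enrolment.
- Description of the control condition/usual care has controls "start accessing the adult HIV clinic at the routine age of transfer at the facility".
- Inclusion and exclusion criteria admit ages 13 to 17, partly to allow "alignment with target ages for routine transfer for healthcare facilities in Nigeria of 15- and 18-year-olds".
- Participant recruitment has each site list its eligible adolescents across that whole age range.

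**Losses.** Sample size estimation needs 15 per site and adds three for a 22% loss. That loss is made up of transfer out (5%), moving away (5%) and "deaths during the study at 7%, and study withdrawal/dropout at 5" percent.

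**Analysis.** Statistical analysis says that "ACT will test the difference in the percentage of study participants completing scheduled clinic visits".

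**The concern.** The intervention runs from enrolment, but the outcome begins a year later. A participant who dies or leaves care in that year has been exposed to the assigned arm and has no post-transfer window in the usual sense. The sample size treats deaths and withdrawals as people to be replaced, although for a retention outcome many of them are the failures the trial is meant to count.

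Whether and when a control reaches transfer also depends on which section is followed. If lost or untransferred participants fall out of the comparison, and do so at different rates by arm, the arms compared are no longer those that were randomised. The result could hide a benefit on death or early drop-out, or create an apparent difference where none exists.

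**Working it through.** **1. The plan's own figure.** From Sample size estimation: 5 + 5 + 7 + 5 = 22%. Then 15 × 0.22 = 3.3, taken as 3; 15 + 3 = 18 per site; 18 × 2 × 6 = 216. The figure reproduces. Since 18 × 0.78 = 14.04, close to 15, the required 15 is a count of participants left after deaths and withdrawals have been taken out.

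**2. How much of the loss is outcome failure.**
- Deaths only: 0.07 × 216 = 15.1.
- Deaths plus withdrawals, if withdrawal means leaving care: 0.12 × 216 = 25.9.

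**3. Post-transfer time for a control under the routine-age wording.** Follow-up lasts 3 years. A control enrolled at exact age *x* at a site that transfers at age *A* has *x* + 3 − *A* years after transfer by month 36. Age at last birthday *a* covers exact ages from *a* to just under *a* + 1.

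| Age at enrolment | Site transferring at 18 | Site transferring at 15 |
|---|---|---|
| 13 | none (−2 to −1 years) | 1 to 2 years |
| 14 | none (−1 to 0) | 2 to 3 years |
| 15 | under 1 year | at or past routine age |
| 16 | 1 to 2 years | past routine age |
| 17 | 2 to 3 years | past routine age |

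Under this wording, controls aged 13 or 14 at an 18-year site have no window, and those aged 15 do not reach the 12-month time point. At a 15-year site, those aged 16 or 17 are already past the routine age. Table 1 would instead transfer all of them at month 12, so a 13-year-old at an 18-year site would transfer at about 14. The full age range at every site, the routine-age rule and a month-12 transfer for everyone cannot all hold.

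**4. What dropping losses would do.** If a proportion *r* of all enrolled is retained and a proportion *L* is dropped, the reported figure is *r*/(1 − *L*). The document gives no retention rates and no losses by arm, so the values of *r* and the arm-specific losses below are assumptions.
- Equal loss of 22%, *r* = 65% in both arms: 0.65/0.78 = 83.3% in each, difference 0.
- Losses of 17% and 27%, *r* = 65% in both arms: 0.65/0.83 = 78.3% and 0.65/0.73 = 89.0%. This is a spurious 10.7 points in favour of the arm with more loss.
- Dropping only pre-transfer losses of 5% and 10%: 0.65/0.95 = 68.4% and 0.65/0.90 = 72.2%, a spurious 3.8 points. For scale, 22% spread evenly over 36 months puts 0.22/3 = 7.3%, or 7.9 of 108 per arm, before transfer.
- The opposite error: suppose the intervention halves death plus drop-out from 12% to 6%, 10% leave the area or site in each arm, and 80% of the rest are retained. Dropping losses gives 80% in both arms. Over all enrolled the figures are 0.78 × 0.80 = 62.4% and 0.84 × 0.80 = 67.2%, so a 4.8-point benefit is hidden. Counting the 10% as retained adds 10 points to both arms and leaves the gap unchanged.

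**5. Change of scale under equal loss.** The scale of the planned 20% effect is not stated. If it means 20 points among those not lost, counting all 22% as not retained makes it 0.78 × 20 = 15.6 points over all enrolled.

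**The case against.** Three stronger readings are tempting, and the document does not support them.

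*That the arms transfer under different rules by design.* Table 1, Data collection and the Abstract set one schedule for both arms, and the inclusion criteria describe controls as observed over the same 12 months. The one-year-younger sentence speaks of participants and of each study facility, so it may be meant for both arms. The 13 to 17 range may then simply cover both site types, and the criteria allow some flexibility in transfer age. What stands is that the sections as written conflict, not that a difference was intended.

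*That deaths and drop-outs are excluded from the analysis.* They are treated as losses only in the sample size. The analysis text refers to study participants and excludes no one, and on Table 1's schedule a participant with no visits after month 12 can be scored as not retained. Detailed handling may sit in an analysis plan that is not shown, so its absence here is not the point. What stands is that the stated inflation treats outcome failures as replaceable, and so points towards an evaluable set without them.

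*That the comparison is biased.* Bias needs both exclusion and loss that differs by arm, and neither is established.

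It is also fair that withdrawing from a study is not always leaving care. Only the 7% deaths are firmly in conflict with being retained, and 12 points is an upper reading.

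**Conclusion.** The point holds as a risk built into the stated rules, not as demonstrated bias. The outcome clock starts at a post-randomisation event, the sample size replaces participants whose death or departure from care is non-retention, and the age and transfer rules cannot all be followed.

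Between 7 and 12 of the 22 points of assumed loss (about 15 to 26 of 216) are outcome failures, depending on what withdrawal means. Under the illustrative assumptions, dropping losses gives anything from no distortion with equal loss to about 10.7 points with 17% versus 27%, in either direction. That is large beside an effect of 20 points, if that is what the planned effect means. The document does not allow the actual size or direction to be known. The age-window result rests on reading the eligibility range and the control-arm wording literally. It should be settled before outcomes are seen.

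**What to change.** - Analyse all enrolled participants by the arm of their site.
- Use month 12 after enrolment, Table 1's transfer point, as the common time origin for the outcome in both arms.
- Count death and loss from care at any time from enrolment as not retained.
- Keep withdrawal from the study separate from leaving care, using clinic visit records where consent allows.
- Examine documented transfer-out in a sensitivity analysis.
- Reconcile the inclusion criteria, the intervention and control descriptions, Participant recruitment and Table 1, so that one enrolment and transfer-timing rule applies in both arms. Which rule that is remains for the investigators to decide.
- Restate the sample-size effect and loss allowance on the all-enrolled scale.

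The cost is analysis wording and one clarified criterion. Reported retention will be lower in both arms, and fewer adolescents per site may fit the reconciled criterion.

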### Site selection and randomization

Study sites were selected from among secondary- and tertiary-level PEPFAR-supported healthcare facilities with at least 12 months’ experience in providing comprehensive HIV care and treatment services. Eligible sites were further expected to meet the following criteria:At least 20 ALHIV enrolled in care as of 31 July 2016Separate pediatric and adult HIV care teams and clinicsAt least one dedicated physician and one dedicated nurse for each pediatric and adult HIV clinic

All sites were assessed using a standardized tool to determine whether they met the selection criteria.

Our desire was to meet the suggestions of the Consolidated Standards of Reporting Trials (CONSORT) “extension for cluster designs” checklist in our randomization procedure. To that end, we provide details here of both sequence generation and allocation [29]. Twelve healthcare facilities were selected and randomized 1:1 to the intervention and control arms (Fig. 2). These 12 study sites were pair-matched by geographic location and level of care and then randomly assigned to the intervention group (IG) or to the control group (CG). Particular attention was paid to remove bias of group assignment by concealment at the individual participant level. The randomization of facilities was carried out using scripting language in R (v. 3.3.2) by the project statistician [30]. We first created a random number between 1000 and 10,000 and used the result to seed the group assignment so that the results would be reproducible. Based on the pair-matched locations and level of care, we used the “sample” function to determine which member of each matched facility pair would be assigned to each of CG and IG. Of note, age at transfer for each study site was considered in order to include sites that transferred at 15 years as well as 18 years, according to the results of our survey [14]. All enrolled study participants receiving care at each study site will follow the procedures of their respective randomization arms described below.

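### Losses and refusals are inflated as n × rate, rounded down, so at the protocol's own rates 18 enrolled leave about 14 per site (not 15) and 23 approached yield about 16 consenting (not 18)

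*Protocol article*

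**What the plan says.** The protocol article, under Sample size estimation, starts from the power calculation: "a baseline number of 15 participants per site was needed". It lists four sources of loss: transfer to another facility 5%, moving away 5%, death 7% and withdrawal 5%. It sums them and applies the total: "This results in a total of 22% dropouts, requiring an additional three participants (15 × 0.22) for a total of 18 participants per site".

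Refusal is handled next. The text says "we anticipate a 30% rate for declining to participate" and concludes that "we will need to approach an additional five ALHIV (18 × 0.3) for a total of 23 ALHIV currently enrolled". The 23 is presented as enough to guarantee 18 enrolled at each site. Over two arms and six zones this becomes 276 to approach and 216 consented. The abstract also gives 216 as the trial's size.

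Under Site selection and randomization, one eligibility condition for facilities is "At least 20 ALHIV enrolled in care as of 31 July" 2016.

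**The concern.** Participants are lost from those enrolled, and refusals come from those approached. To finish with n after a proportion r is lost, one must start with n/(1 − r). The protocol starts with n + n × r, which is always smaller, and then rounds each increment down where a sample size is normally rounded up.

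This matters because the power claim of at least 80% is attached to 15 per site, and the enrolment figure of 18 is meant to protect that 15. If 18 does not leave 15 at the protocol's own loss rate, the stated power belongs to a sample that the plan does not expect to have. If 23 approached do not give 18 consenting at the protocol's own refusal rate, sites working to a list of 23 will expect to fall short of their quota.

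**Working it through.** **Inputs (all from Sample size estimation).** 15 needed per site; losses 5% + 5% + 7% + 5% = 22%; refusal 30%; 12 sites. The 15 is taken as given.

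**Reproducing the protocol's figures.**
- 15 × 0.22 = 3.3, rounded down to 3; 15 + 3 = 18 enrolled.
- 18 × 0.30 = 5.4, rounded down to 5; 18 + 5 = 23 approached.
- 18 × 12 = 216 and 23 × 12 = 276.

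The figures reproduce exactly, so the method used is not in doubt.

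**Checking them against the stated rates.**

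| Step | Start | Kept | Result per site | Needed | Total | Needed |
|---|---|---|---|---|---|---|
| Loss | 18 | 0.78 | 14.04 | 15 | 168.5 | 180 |
| Refusal | 23 | 0.70 | 16.1 | 18 | 193.2 | 216 |

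The shortfalls are 11.5/180 = 6.4% and 22.8/216 = 10.6%. Put the other way, 18 covers a loss of only 1 − 15/18 = 16.7%, and 23 covers a refusal rate of only 1 − 18/23 = 21.7%.

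**Is it only the rounding?** No. Rounding the same increments up gives 19 and 24, and 19 × 0.78 = 14.8 and 24 × 0.70 = 16.8 are still below 15 and 18.

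**Is it the summing of the losses?** No. Compounding them gives 1 − 0.95 × 0.95 × 0.93 × 0.95 = 20.3%. Then 18 × 0.797 = 14.35, still below 15, and 15/0.797 = 18.8 calls for 19.

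**Correct inflation.**
- Enrolment to keep 15: 15/0.78 = 19.2, so 20 per site (240).
- Approaches for 20: 20/0.70 = 28.6, so 29 per site (348).
- Approaches if 18 is kept: 18/0.70 = 25.7, so 26 per site (312).

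The 26 belongs with 18 enrolled and the 29 with 20 enrolled; 20 and 26 are not one plan.

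**Effect on power.** With the protocol's intra-class correlation of 0.05, the design effect is 1 + (m − 1) × 0.05.
- At m = 15: 6 × 15/1.70 = 52.9 effective participants per arm.
- At m = 14.04: 6 × 14.04/1.652 = 51.0 per arm, about 4% fewer.

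The protocol gives no control retention rate, so a range is assumed, with a 20-point absolute difference and a two-sided 5% test of two proportions:

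| Assumed control rate | Power, 15 per site | Power, 14.04 per site |
|---|---|---|
| 40% | 54.0% | 52.4% |
| 50% | 55.7% | 54.1% |
| 60% | 61.5% | 59.9% |
| 70% | 73.7% | 72.0% |
| 75% | 83.2% | 81.7% |

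The drop is 1.5 to 1.7 points across the range. A one-sided test gives 1.0 to 1.4 points. Only the differences are of interest here. The levels depend on the assumed rate and are not a test of how the 15 was derived.

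**The case against.** The arithmetic cannot be defended, but several inferences that a reader might draw from it go too far.

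- **That the trial will end with about 151 participants (12.6 per site).** Chaining both errors gives 193.2 × 0.78 = 150.7, with a power loss of about 4 to 5 points on the assumptions above. This requires approaches to stop at 276 whatever the consent rate. The documents do not say so: 216 consented is the stated target, and Participant recruitment describes site lists of eligible adolescents and a recruitment window of several months, with no cap on approaches. The figure is a worst case only.
- **That sites will run out of adolescents because the site criterion is 20.** The criterion is a minimum for site eligibility, dated about 11 months before recruitment began. Site counts are not given. A floor below 23, or below 26, is a fair feasibility remark but does not demonstrate a shortfall.
- **That 168 is the number analysed for the primary outcome.** Retention is defined by clinic visits made, so some of those lost might be counted as not retained and stay in the denominator. The article does not settle this. The sample size section does, however, treat the whole 22% as losses to be made up, so 14 per site is a fair check of its own logic.
- **That the stated power is badly compromised.** One participant per site is a small loss, and clustering dampens it further.

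These points limit the consequences. They do not rescue 18 or 23 as the answers to the stated inputs.

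**Conclusion.** Wrong as written, of moderate severity. The enrolment and approach figures contradict the rates from which they are derived. The expected number remaining after losses is about 14 per site (168 in total), where 15 (180) is required. Approaching 23 per site yields about 16 consenting (193 in total), where 18 (216) is said to be secured. The conclusion rests only on the protocol's 22% and 30%, and it survives compounding the losses and rounding the increments up.

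The effect on power is small, roughly 1.5 to 2 points, and depends on an assumed control rate. The refusal error affects the length of the approach list, not the enrolment target.

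**What to change.** Choose one consistent plan and state it.

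1. **Keep 216 enrolled.** Correct the approach target to 26 per site (312), give the number expected after losses as about 14 per site (168), and restate power on that number, with the control retention rate that it assumes.
2. **Keep 15 per site after losses.** Enrol 20 and approach 29 per site (240 and 348).

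The first is cheaper: a text correction, 36 more adolescents to approach (312 − 276), and a slightly lower stated power. The second adds 24 participants (240 − 216) and 72 approaches (348 − 276). In either case, show the n/(1 − rate) formula and round up. A sentence noting whether each selected site has enough eligible adolescents for the revised approach target would deal with the feasibility remark on the site minimum. Trial status shows recruitment open until 1 December 2017, so when the article was written the approach lists could still be lengthened.
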